### Study Variables

The primary outcome in this study is symptomatic SARS-CoV-2 infection, defined as a positive RT-PCR test within 10 days from the onset of influenza-like illness. The secondary outcome in this study is fatal SARS-CoV-2 infection, defined as death within 30 days after a positive RT-PCR test result [24]. Meanwhile, the primary exposure in this study was vaccination status, which can be classified as unvaccinated, dose 1 or partial vaccination, dose 2 or primary vaccination, and booster dose. People without any vaccination entries after data linkage with the PCARE Vaksin dataset at the end of each period of interest will be classified as unvaccinated persons. For vaccinated people, we will only consider the last vaccination data entry that happened before the patients’ index RT-PCR test date.

Several covariates should be assessed as potential confounders in the study, such as age in years at the index test date, gender, calendar week of the RT-PCR collection during the period of interest, living in impoverished neighborhoods, presence of any comorbidities, occupation, and reinfection status. The calendar week of the RT-PCR collection during the period of interest will be presented as a whole number starting from week 1 as the start of the period of interest. Living in an impoverished neighborhood will be presented as a dichotomous variable. People will be classified as living in an impoverished neighborhood if their neighborhood number at the subdistrict level is listed as one of the impoverished neighborhoods in the 2018 Jakarta Governor’s regulation concerning improving the quality of settlements in residential areas. Occupation will be presented as categorical variables that consist of health care worker, public or government official, and civilian. Reinfection or people with previous SARS-CoV-2 infections will be presented as a dichotomous variable. People with a previous positive RT-PCR SARS-CoV-2 result that occurred more than 90 days after the current case will be classified as people with a previous SARS-CoV-2 infection [25].

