To control for unmeasured confounders [26], such as societal preventive measures or the changing dynamic of the viral transmission within the community, this study will match each case with a control using a ratio of 1:2 by matching for age within 10 years of the case’s age, gender, and the calendar week of the RT-PCR collection during the period of interest. The matching procedure will be assessed with standardized mean differences, with values less than 0.1 indicating sufficient matching [27,28].

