### Statistical Analysis

We adopted our VE analysis from the Interim Guidance of Evaluation of COVID-19 Vaccine Effectiveness by the World Health Organization, where the final estimate of absolute VE (aVE) will be determined by calculating the adjusted odds ratio (aOR) for vaccination using the formula aVE = (1 – aOR) × 100% [24]. Unconditional multivariable logistic regression will be used to analyze the aOR of having symptomatic and fatal SARS-CoV-2 infection between the unvaccinated and vaccinated participants. We will perform separate analyses for the Delta- and Omicron-dominant periods. Furthermore, within each period, we will also analyze each vaccinated person separately by their vaccine brand or platform and vaccination doses, such as dose 1, dose 2, or booster. For the main aVE analyses, we will include only vaccinated people with the last dose 1 or dose 2 vaccination date within 14-90 days or with the last booster dose within 7-90 days before their index test date and compare them to the unvaccinated people.

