One main logistic model will be assembled by forward inclusion, and only covariates with less than 20% missing data will be considered to be included in the model building. Assessment for confounders and effect modifiers will be performed with the Wald test and by observing the change in the primary exposure coefficient SE. Covariates that act as confounders will be included in the model. If effect modification is present, it is essential to report VE and CIs for each subgroup individually. The linearity between continuous variables and the log odds of having symptomatic SARS-CoV-2 infection will be assessed, and the continuous variables will be modified into categorical variables if necessary. The overall fit of the final multivariate logistic regression model will be assessed with Hosmer and Lemeshow goodness-of-fit test [30], as matching might incur matching-related bias from the cases and controls having similar exposure, thus underestimating the aVE. We will also perform conditional logistic regression as a sensitivity analysis for measuring the aVE estimation against symptomatic SARS-CoV-2 infection or our primary objectives [31,32]. Furthermore, for the analysis of the Omicron period, we will perform an additional analysis of relative VE (rVE) by comparing recipients of one booster dose to recipients of the 2 doses who were eligible to receive the booster dose. The rVE will be calculated using the formula rVE = [(aVE from booster dose – aVE from 2 doses and eligible for booster)/(1 – aVE from 2 doses and eligible for booster)] × 100%. For the rVE analyses, we will include only people whose last booster dose was within 7 to 90 days before their index test date and compare them to people whose last 2-dose vaccination date was ≥90 days before their index test date [24].

This study will also conduct subgroup analyses based on the time between the last vaccination date and test index date to assess for waning of immunity (Table 2). These subgroup analyses will be conducted separately for each wave and vaccine brands or regimens. Similar to the main analysis, each vaccinated subgroup will be compared to unvaccinated people.

**Table 2 table2:** Subgroup analysis based on time since last vaccination.

Subgroup	Description
1	7-14 days between the last vaccination dose and index test date
2	14-28 days between the last vaccination dose and index test date
3	28-56 days between the last vaccination dose and index test date

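### Confounders are screened by the change in the SE of the exposure coefficient, which does not measure confounding, and the matching factors are not guaranteed a place in the unconditional model

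*Protocol article*

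**What the plan says.** All places are in the Methods of the protocol article.

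- **Model building (Statistical Analysis).** "One main logistic model will be assembled by forward inclusion, and only covariates with less than 20% missing data will be considered". The selection rule is "Assessment for confounders and effect modifiers will be performed with the Wald test and by observing the change in the primary exposure coefficient SE", followed by "Covariates that act as confounders will be included in the model". No covariate is stated to be forced in.
- **Candidates (Study Variables).** "Several covariates should be assessed as potential confounders in the study, such as age in years at the index test date, gender, calendar week". The list continues with impoverished neighborhood, comorbidity, occupation and reinfection status.
- **Form of week (Study Variables).** "The calendar week of the RT-PCR collection during the period of interest will be presented as a whole number starting from week 1".
- **Matching (Study Variables).** Cases are matched to controls "using a ratio of 1:2 by matching for age within 10 years of the case’s age, gender, and the calendar week of the RT-PCR collection". These are the first three candidates on the list above.
- **Primary model (Statistical Analysis).** "Unconditional multivariable logistic regression will be used to analyze the aOR of having symptomatic and fatal SARS-CoV-2 infection".
- **Sensitivity model (Statistical Analysis).** Conditional logistic regression is planned for symptomatic infection only.

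**The concern.** A confounder is recognized by what its inclusion does to the exposure coefficient. The SE of that coefficient responds mainly to the covariate's correlation with vaccination. It can rise sharply for a covariate that confounds nothing and barely move for one that confounds strongly. The Wald test asks only whether a covariate is related to case status. Neither criterion looks at the aOR.

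The matching factors are a special case. Matching makes age, gender and week nearly unrelated to case status on their own, so an outcome-based screen has little to find. They remain related to vaccination, and an unconditional model that leaves them out pulls the odds ratio toward 1. Since aVE is computed directly from the aOR, that error passes straight into the study's main result.

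**Working it through.** **1. The planned size.** The Sample Size section gives about 5000 cases and 10,000 controls per brand-and-dose analysis, for VE 50%-90%, coverage 20%-90%, precision ±5% and alpha 0.05. A standard precision formula reproduces this at its most demanding corner (VE 50%, coverage 20%):

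- p0 = 0.20; p1 = 0.5×0.20/(0.80 + 0.5×0.20) = 0.111
- cases = 1.96² × 0.5² × [1/(p1q1) + 1/(2·p0q0)] / 0.05² = 3.84 × 0.25 × (10.125 + 3.125) / 0.0025 ≈ 5090, or about 15,270 in total

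The sample size is not in dispute. The checks below use 5000 and 10,000.

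**2. Does the SE change track confounding?** Logistic models were fitted with and without one binary covariate (20 replicates, true VE 50%). The covariate strengths are assumptions, not figures from the protocol.

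| Covariate | VE without → with | Change in coefficient | Change in SE |
|---|---|---|---|
| Confounder: 15% prevalence, 25% vaccinated with it vs 50% without, outcome OR 3 | 57.7% → 49.6% | about 20% | +3.3% |
| Confounder: OR 2 with vaccination, OR 2 with outcome | 44.4% → 50.8% | 21% | +3.5% |
| Outcome only: OR 3 | 48.5% → 49.6% | 3.5% | +3.1% |
| Vaccination only: 30% vs 80% vaccinated, outcome OR 1 | moves 0.1 point | about 0 | +15.7% |
| Vaccination only: OR 20 | 50.4% → 50.3% | −0.2% | +28% |

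The first coefficient change is (0.860 − 0.685)/0.860 = 20%, from ln(1 − 0.577) = −0.860 and ln(1 − 0.496) = −0.685. By SE change, the two non-confounders tied to vaccination rank far above both real confounders. One real confounder cannot be told apart from the outcome-only covariate (3.5% against 3.1%).

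**3. What does the Wald test rescue?** For the first confounder its z was about 25. At 5000 cases every unmatched true confounder tested was retained.

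**4. What happens to a dropped matching factor?** Each study period is 92 days, or about 13 weeks. Assume cases spread evenly over 13 weeks, exact 1:2 matching on week within the analysis set, and a true OR of 0.5 each week. With coverage c in controls, coverage in cases is 0.5c/(1 − 0.5c). Averaging both over the weeks gives the expected OR without week:

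| Assumed coverage | Mean in controls | Mean in cases | OR without week | VE without week | Simulated VE |
|---|---|---|---|---|---|
| Linear 20% to 60% | 0.400 | 0.258 | (0.258/0.742)/(0.400/0.600) = 0.521 | 47.9% | 48.2% |
| Linear 5% to 80% | 0.425 | 0.299 | (0.299/0.701)/(0.425/0.575) = 0.577 | 42.3% | 42.7% |
| Hump 20%-80%-20% | 0.551 | 0.407 | (0.407/0.593)/(0.551/0.449) = 0.56 | 43.9% | 43.9% |

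The bias is 2.1, 7.7 and 6.1 points by expected counts, and 1.8, 7.3 and 6.1 in simulation, always toward zero. Week entered as categories restores about 50%.

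**5. Would the screen find week?** Tested alone in matched data, week was non-significant in every replicate. Tested beside vaccination with 5000 cases:

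- Linear week was retained under both monotone curves.
- Under the hump, linear week was missed in every replicate, with an SE change of 0%. The curve is symmetric, so a straight line has nothing to fit.
- Week categories were missed in 90% of replicates under the 20% to 60% curve.

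With 500 cases, the joint test of week categories was missed in every replicate under all curves.

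A rise and fall is plausible here. The main analysis keeps only people whose last dose 1 or dose 2 was 14-90 days earlier, so people leave the exposed group as time passes.

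**The case against.** **Unmatched confounders are largely safe.** A reader might infer that the rule will omit real confounders in general. The documents do not support that at the planned size: the rule includes the Wald test, and step 3 shows it keeps them. Wrongly admitting a non-confounder costs precision but hardly moves VE. This objection stands and narrows the point.

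**The primary model may not use the matched subset.** Data Sources says a matched subset is created from the final dataset, Sample Size expects 400,000-900,000 people overall, and Statistical Analysis does not say which dataset the unconditional model uses. Study Variables and the bias table (Table 3) point toward matched data. The question is open, so the bias in step 4 is conditional. On the unmatched reading, adjustment is the only control for the three factors, and the SE criterion is still wrong.

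**The size rests on assumed curves.** Another check, with other assumed roll-outs and the matched data cut to one brand and dose, gave VE of 48.3-49.3%, a bias of 0.7 to 1.7 points. A 5% to 95% roll-out gives 37.9%, a bias of 12 points. Neither is in the protocol. Linear week is found under monotone coverage, and the plan checks linearity. That check may not help, since matched data show a flat marginal log odds by week. Conditional regression does protect the symptomatic outcome, but only as a sensitivity analysis.

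**Other stronger readings fail.** One might infer different adjustment sets by brand and wave, but the plan speaks of one main model. One might also infer that the Hosmer-Lemeshow test is meant to detect matching bias. The clause about matching may belong to the next sentence, on conditional regression.

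**It may be a slip** for coefficient and SE. The text would still need correcting, and as printed it uses the SE alone.

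**Conclusion.** The point holds in limited form. The SE criterion is fixed in the protocol and does not measure confounding, whatever assumptions are made about coverage. The matching factors are left as candidates in an unconditional model, with nothing that keeps them there.

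If that model is fitted to matched data and week is dropped or entered linearly under non-monotone coverage, aVE falls by about 2 to 8 points at a true VE of 50%. The upper end exceeds the ±5% precision the study was sized for. That size rests on the three assumed curves, an even spread of cases and matching that holds within the analysis set; gentler or steeper curves give less or more. Fatal infection is the more exposed outcome, because no conditional analysis is planned for it.

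**What to change.** - Delete the SE criterion and the forward Wald screen for confounders.
- Pre-specify one adjustment set for all aVE models from the covariates already listed: age, gender, calendar week as categories, impoverished neighborhood, comorbidity, occupation and prior infection, subject to the existing 20% missing-data rule.
- Keep age, gender and categorical week in every unconditional model, including the one for fatal infection.
- If any screening is retained, base it on the change in the aOR, and reserve Wald tests for interaction terms.

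The cost is a few extra parameters, mainly the week categories, and slightly wider intervals in small subgroups. In the step 4 scenarios at 5000 cases, categorical week raised the SE of the exposure coefficient by 3% to 13%. The Results section says analysis is under way, so any model already selected by the present rule would need refitting. No change in sample size follows.

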## Methods

### Study Design and Setting

This population-based study adopts a test-negative case-control design to analyze COVID-19 VE against symptomatic and fatal SARS-CoV-2 infection from available health care datasets in the Special Capital Region of Jakarta, one of the provinces with the highest population density (15,900 people per km^2^ in 2020) and case rate per population relative to other regions in Indonesia [9]. Despite its robust development and economic growth, the contrast between rich and poor neighborhoods was highly prevalent in many parts of Jakarta’s districts [8,10].

This study will estimate VE against COVID-19 during the period of interest, which were the COVID-19 waves associated with the Delta and Omicron variants, from June 1 to August 31, 2021, and January 1 to April 2, 2022, respectively. Within each of these periods, a cycle of sustained upward and downward trends of the test positivity rate was observed [11-15] (Figure 1). Furthermore, the Delta and Omicron variants were estimated to be responsible for around 90% of SARS-CoV-2 infections in Jakarta during these two periods [14,16].

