**Figure 1 figure1:**
[figure not shown]
Trend of the national COVID-19 positivity rate in Indonesia from 2021 to 2022. This modified image is cited from Our World in Data.

During the Delta and Omicron periods, several brands of COVID-19 vaccines were introduced in Jakarta for vaccine rollout, such as AstraZeneca, SinoVac-CoronaVac Biofarma, Covovax-Novovax, Indovax, Johnson & Johnson, Moderna, Sinopharm BBIBP, and Pfizer (Table S1 in Multimedia Appendix 1) [17]. Among these COVID-19 vaccines, Coronavac-Sinovac was the earliest COVID-19 vaccine to be introduced in January 2021 and used for mass vaccinations of doses 1 and 2, followed by AstraZeneca, Sinopharm, Pfizer, and Moderna in August 2021 [18,19]. Booster vaccinations 6 months after the 2-dose primary vaccination with Moderna and Pfizer vaccines were initially introduced to health care workers in July 2021, followed by the approval of the AstraZeneca vaccine as a booster in the national vaccination program in January 2022 [20,21]. To expedite the booster vaccination coverage, the timeline for booster administration was shortened to 3 months after the 2-dose primary vaccination, and additional inactivated COVID-19 vaccines, such as SinoVac and Sinopharm, were included in the national booster program [22]. Different from Pfizer, Moderna, and AstraZeneca, these inactivated COVID-19 vaccines were only approved as boosters for patients who received similar vaccine platform for their primary vaccination regimen [23]. Until the end of the Omicron period, all of the distributed COVID-19 vaccines in Jakarta were developed from the ancestral strain of SARS-CoV-2.

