4	56-90 days between the last vaccination dose and index test date
5	90-180 days between the last vaccination dose and index test date
6	>180 days between the last vaccination dose and index test date

A 2-sided *P* value derived from the multivariable logistic regression analysis will be used to assess VE. Data linkage and data cleaning will be performed in Google Collaboratory with the Python programming language. Furthermore, the Statsmodel library package will be used for statistical analysis [33].

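### In the Omicron window, mRNA booster subgroups beyond 90 days come predominantly from the early health care worker roll-out, so time since booster is confounded with occupation

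*Protocol article*

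**What the plan says.** All places are in the Protocol article, Methods.

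- **Windows** (Study Design and Setting): the Delta and Omicron periods run "from June 1 to August 31, 2021, and January 1 to April 2, 2022, respectively".
- **Booster timeline** (same section, paragraph after Figure 1): Moderna and Pfizer boosters "were initially introduced to health care workers in July 2021". The wider programme came some six months later; its AstraZeneca step is dated to January 2022. Inactivated boosters are described after that, as a further addition to the national booster programme, without a date.
- **Waning analysis** (Statistical Analysis, Table 2): "These subgroup analyses will be conducted separately for each wave and vaccine brands or regimens", and "each vaccinated subgroup will be compared to unvaccinated people". Subgroup 5 is "90-180 days between the last vaccination dose and index test date" and subgroup 6 is ">180 days between the last vaccination dose and index test date". Boosters are not excepted.
- **Main booster analysis** (Statistical Analysis): this takes people "with the last booster dose within 7-90 days before their index test date", so it does not use subgroups 5 and 6.
- **Occupation**: Study Variables lists it as a potential confounder with three categories, one being health care worker. It is not a matching factor. Table 1 shows it only under PCARE Vaksin, the register of vaccine recipients.

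**The concern.** A waning series is read as one population followed along time since dose. For boosters in the Omicron window the dates do not allow that. Boosters from the 2022 programme can appear only at short intervals, and the long intervals must be filled by people boosted earlier, in a roll-out that began with health care workers. That group may differ from the general public in exposure, in access to testing and in reasons for being tested.

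A change in VE between the early and late booster subgroups could therefore reflect who was boosted early rather than loss of protection. It could also hide a real loss. VE by time since last dose is a stated secondary objective, and the subgroup analysis is said to be there to assess waning, so the estimate would be reported under that name.

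**Working it through.** The plan gives no counts or precision for the booster time strata, so there is no figure of its own to reproduce here. The sample-size figure of about 15,000 per brand-and-dose analysis plays no part.

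**1. How old can a 2022 booster be?**
Inputs: Omicron window 1 January to 2 April 2022 (92 days); national-programme booster dated January 2022, day not given.

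- Booster on 1 January, test on 2 April: 91 days.
- Latest booster date that gives 90 days on 2 April: 2 April minus 90 days = 2 January 2022.
- Counting every booster-day and test-day pair inside the window (day pairs, not people):

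| Programme start | Largest gap | Pairs at 90 days or more |
|---|---|---|
| 1 January | 91 days | 3 of 4278 (0.07%) |
| 2 January | 90 days | 1 of 4186 |
| 3 January | 89 days | 0 |
| 15 January | 77 days | 0 |
| 31 January | 61 days | 0 |

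No pair exceeds 180 days. To be more than 180 days past a booster on 2 April, a person must have been boosted by 3 October 2021.

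**2. Who can fill subgroups 5 and 6?**
A booster given in July 2021 is 154 to 184 days old on 1 January 2022 and 245 to 275 days old on 2 April. The early mRNA roll-out therefore falls in subgroups 5 and 6 throughout the window. A booster that entered use in January 2022 reaches subgroup 5 at most at its 90-91 day edge.

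**3. Is there a clean break at 90 days?**
No. A booster given on 1 January 2022 reaches 56 days on 26 February. From 1 January to 25 February, 56 of the 92 window days, subgroup 4 (56-90 days) can hold only pre-2022 boosters. The mix of early and later recipients already shifts inside subgroup 4.

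**4. Delta.**
From 1 July to 31 August 2021 is 61 days. Booster subgroups 5 and 6 are empty in Delta, and any Delta booster estimate rests mainly on the health care worker roll-out.

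**5. Does the planned adjustment reach the problem?**
Occupation may enter the model by forward inclusion if less than 20% of its values are missing. People are classed as unvaccinated because they have no PCARE Vaksin entry by the end of the period, and Table 1 names no other source for occupation. On the listed sources it is unknown for the reference group. If unvaccinated people are 20% or more of an analysis, the plan's own rule drops the covariate.

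For spurious waning, Table 3 relies on separate variant periods, calendar-week matching and stratification by time since dose. None of these concerns who was boosted early.

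**6. Size (illustration).**
Let r be the odds ratio of a positive test for health care workers against others at equal vaccination status, among symptomatic tested people. This is an assumption; the documents give no value. Take a subgroup made up wholly of health care workers, a reference group with none, no effective adjustment and no true waning:

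apparent VE = 1 − (1 − true VE) × r

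With true VE 60%, so 1 − VE = 0.40:

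| r | 0.40 × r | Apparent VE |
|---|---|---|
| 0.5 | 0.20 | 80% |
| 0.8 | 0.32 | 68% |
| 1.0 | 0.40 | 60% |
| 1.2 | 0.48 | 52% |
| 1.5 | 0.60 | 40% |
| 2.0 | 0.80 | 20% |

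A subgroup only partly made up of health care workers would show a smaller shift.

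**The case against.** The strongest reply is that occupation is already a planned confounder and that VE is to come from an adjusted odds ratio. That would answer the point if occupation were known on both sides of the comparison. On the listed sources it is not. Even if it were obtained, a subgroup that is nearly all health care workers leaves little within-group variation to adjust on, and the separation would depend on unvaccinated health care workers.

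Other objections stand and limit the point:

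- **Exclusivity.** A reader might infer that subgroups 5 and 6 contain health care workers only, or that everyone boosted in Delta was one. The article says only that mRNA boosters began with that group, and it ties January 2022 to the AstraZeneca approval. It does not say when mRNA boosters reached others.
- **Pure comparison of occupations.** Time since booster differs as well, so the two are confounded; neither replaces the other. Nor is there a clean switch at 90 days (step 3).
- **Brand.** A reader might add that booster brand changes across the strata too. The subgroups are run separately by brand or regimen, so within a brand-specific series it does not. For AstraZeneca and inactivated boosters the late strata give practically no data, hence no false waning.
- **Direction.** It is tempting to conclude that waning will be exaggerated. In a test-negative design r may lie below 1, for instance through easier access to testing, and waning would then be masked.
- **Table 3.** Its comment on exposure risk concerns differences over calendar time. It does not claim to deal with occupation.

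**Conclusion.** The point holds for mRNA boosters in the Omicron window. Subgroups 5 and 6, and partly subgroup 4, confound time since booster with occupation, and the plan's listed data do not support the adjustment that would separate them. For AstraZeneca and inactivated boosters, subgroups 5 and 6 are practically empty.

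The calendar limit of 91 days is exact, given a programme start no earlier than 1 January 2022. That the early-boosted group is predominantly health care workers is the natural reading of the article's timeline but is not stated outright. The shift of up to 40 points downward or 20 upward depends on the assumed r of 0.5 to 2.0 and a true VE of 60%; the documents fix neither its size nor its sign.

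Main booster VE and relative VE in Omicron, which use boosters at 7-90 days, and waning after dose 1 or dose 2 are outside this conclusion. What is affected is a secondary objective, in a few strata of one wave, but there the estimate cannot be read as waning.

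**What to change.** 1. Do not interpret booster subgroups 5 and 6 against unvaccinated people as waning.
2. Limit the general-population booster series to 90 days or less. Split boosted people by PCARE occupation, and note that occupation is not available for the unvaccinated reference group. For that reason the whole comparison cannot simply be restricted to people who are not health care workers.
3. Assess longer intervals among boosted health care workers only, comparing more than 90 days with 7-90 days after the booster, within brand or platform and adjusted for calendar week. PCARE Vaksin is designed to hold occupation for all of them.
4. State that general-population booster waning beyond 90 days cannot be estimated in this window, and that Delta booster VE rests mainly on health care workers.

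The cost is wording plus a restriction on a field already held. The waning conclusion becomes narrower, and beyond 90 days the estimate is relative to recent boosters rather than absolute. The 7-90 day comparison group of health care workers may be small, since in this window it can include only those boosted from 3 October 2021 (90 days before 1 January) to 26 March 2022 (7 days before 2 April). Its size should be reported.

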### Sample Size

The calculation formula for the sample size used in this study will follow the methodology described by O’Neill [29]. Assuming vaccination coverage between 20%-90%, a precision of ±5%, a type 1 error rate of 0.05, and an anticipated VE of 50%-90%, the minimum sample size needed for each specific COVID-19 vaccine brand and dose VE analysis is roughly around 15,000, with 5000 cases and 10,000 controls [24,29] (Table S4 in Multimedia Appendix 1).

We expect to analyze 400,000-900,000 people after the aggregation of all datasets. Therefore, we should have enough data to conduct the VE analyses for each specific COVID-19 brand and regimen in our final dataset. We will compare the proportion of COVID-19 vaccines received by eligible people in our dataset during each period of interest to those reported by the Ministry of Health [17] (Table S1 in Multimedia Appendix 1). Furthermore, we will exclude people who received COVID-19 vaccine brands with vaccination coverage of less than 20%, as these vaccines are usually distributed briefly in the population or only available to specific subgroups within the community. Moreover, we might consider combining different COVID-19 vaccine brands with the same platform into one group to decrease the required sample size, especially for the subgroup VE analysis [24].

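### Impoverished neighborhood is set for whole neighborhoods but tested as if people were independent: its Wald test over-rejects, and VE intervals may be somewhat too narrow

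*Protocol article*

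**What the plan says.** **Model and tests (Statistical Analysis).** The main model is unconditional multivariable logistic regression, fitted separately by wave, by brand or platform, and by dose. A 2-sided P value "derived from the multivariable logistic regression analysis will be used to assess VE". On covariates: "Assessment for confounders and effect modifiers will be performed with the Wald test", together with the change in the standard error of the exposure coefficient. Where effect modification is found, VE is to be reported by subgroup. Conditional logistic regression is a sensitivity analysis.

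**The covariate (Study Variables).** People count as living in an impoverished neighborhood "if their neighborhood number at the subdistrict level is listed as one of the impoverished neighborhoods" in a 2018 regulation. The variable is therefore constant within a neighborhood.

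**Sizing (Sample Size).** The assumptions are coverage of 20%-90% and "a precision of ±5%, a type 1 error rate of 0.05, and an anticipated VE of 50%-90"%. Each brand-and-dose analysis then needs "roughly around 15,000, with 5000 cases and 10,000 controls".

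**Clustering.** The article mentions no cluster-robust variance, random effect or design effect. Matching uses age, gender and calendar week only. Domicile address is required for linkage (Data Sources).

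**The concern.** Model-based standard errors from logistic regression are valid when people are independent given the covariates. The outcome here is a transmissible infection in one dense city, and the article stresses that city's contrast between rich and poor neighborhoods. Residual correlation within neighborhoods and households is therefore to be expected.

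The problem is sharpest for a covariate fixed at neighborhood level. Information about it comes mainly from the number of neighborhoods, whereas the ordinary Wald test counts people. Matching and the conditional model do not repair this, because matched sets are neither neighborhoods nor households.

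Two things are at stake. An effect of impoverished neighborhood could be reported as established when neighborhoods merely differ from one another. Less strongly, VE intervals and the test that triggers subgroup VEs could be too optimistic.

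**Working it through.** **1. The plan's own figure.** Worst case in the stated ranges: coverage among controls p0 = 0.20, VE = 50% (OR = 0.5), half-width d = 0.05, two controls per case.
- p1 = OR·p0/(1 − p0 + OR·p0) = 0.10/0.90 = 0.111.
- n(cases) = z²[1/(p1q1) + 1/(2p0q0)]/L² = 3.84 × (10.125 + 3.125)/L² = 50.9/L².
- L = d/OR = 0.10 gives 5090 cases. L = asinh(0.10) gives 5107.
- With two controls each, the totals are 15,270 and 15,321.

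The stated 5000 and 10,000 are reproduced by a formula for independent people, so the sizing has no allowance for clustering.

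**2. The neighborhood term.** For a covariate constant within clusters of m people, with outcome ICC ρ, the design effect is D = 1 + (m − 1)ρ. The true type I error of a nominal 5% test is 2·P(Z > 1.96/√D). Both m and ρ are assumptions.

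| m | ρ | D | type I error |
|---|---|---|---|
| 30 | 0.01 | 1.29 | 8% |
| 50 | 0.01 | 1.49 | 11% |
| 50 | 0.02 | 1.98 | 16% |
| 150 | 0.01 | 2.49 | 21% |
| 150 | 0.02 | 3.98 | 33% |
| 200 | 0.02 | 4.98 | 38% |

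Simulation checks this: 15,000 people, 400 runs per setting, no true neighborhood effect.
- 500 neighborhoods of 30: the ordinary test rejected 10%, 14% and 16% at outcome ICCs of 0.012, 0.027 and 0.058.
- 150 neighborhoods of 100: it rejected 16%, 23% and 37% at the same ICCs.
- Cluster-robust tests rejected 4-7% in these settings.

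The Monte Carlo error near 5% is √(0.05 × 0.95/400) = 1.1 points. Over ICCs of 0.01-0.02 and 30-200 people, roughly 10-35% is a fair summary.

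**3. VE.** Vaccination varies within clusters, so both correlations enter: D = 1 + (m − 1)·ρ(uptake)·ρ(outcome), and the standard error is understated by √D.

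| Cluster | ρ(uptake), ρ(outcome) | D | √D | coverage of a 95% interval |
|---|---|---|---|---|
| neighborhood, m = 50 | 0.02, 0.02 | 1.02 | 1.01 | 94.8% |
| neighborhood, m = 50 | 0.05, 0.05 | 1.12 | 1.06 | 93.6% |
| neighborhood, m = 150 | 0.02, 0.02 | 1.06 | 1.03 | 94.3% |
| neighborhood, m = 150 | 0.05, 0.05 | 1.37 | 1.17 | 90.6% |
| household, m = 3 | 0.3, 0.2 | 1.12 | 1.06 | 93.6% |
| household, m = 3 | 0.5, 0.3 | 1.30 | 1.14 | 91.4% |

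Simulation was milder. The ratio of empirical to model-based standard error was 0.97-1.04 with both ICCs at 0.01-0.06. In one setting with households of three (ICCs of 0.30 for outcome and 0.41 for uptake) it was 1.07, with coverage of 95%. It reached 1.10-1.20 when VE varied between neighborhoods (SD of the log odds ratio 0.2-0.3) with 100 people in each.

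**4. The interaction test.** With constant VE and clustering at neighborhood level only, the ordinary vaccine-by-neighborhood test rejected about 4-8% across simulation sets. With household clustering, or VE varying between neighborhoods, it rejected about 9-11%.

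**The case against.** **The article fixes no variance estimator, and a condensed article may leave that to the full plan.** This stands in part: that every P value assumes independence is inferred from silence. But the article does fix the model, the source of the P value and the Wald test, and it defines a covariate set for whole neighborhoods. Followed as written, that rule gives an anti-conservative test of that covariate.

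**Impoverished neighborhood is a candidate confounder and no objective tests it.** This is fair. Admitting it too readily does little harm to VE, and a second criterion is also used. The harm lies in reporting a neighborhood effect as significant and, to a lesser degree, in subgroup VEs triggered by the interaction test.

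**Stronger readings that a reader might infer are not supported:**
- *That VE intervals are certainly too narrow.* The effect depends on a product of two ICCs and is close to nil for small clusters with modest correlation.
- *That precision falls from ±5 to about ±7.9 points.* That needs D = 1 + 1499 × 0.05 × 0.02 = 2.5. But ±5 belongs to the minimum of 15,000 people, and 1500 per neighborhood would leave 15,000/1500 = 10 neighborhoods.
- *That one Wald test counts 400,000-900,000 people.* That range is for all aggregated data. Analyses are split by wave, brand or platform, dose and time window.
- *That a VE difference by neighborhood would readily be declared on clustering alone.* The 10-35% applies to the main effect. The interaction test is near nominal in the simple case.

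**Conclusion.** The point holds for the neighborhood term. Its stated test rejects roughly 10-35% of the time at a nominal 5%, given outcome ICCs of about 0.01-0.02 and 30-200 tested people per neighborhood. For VE it holds only conditionally. The standard error is nearly correct with small clusters and modest correlation. It is understated by about 10-20% if uptake or infection clusters strongly, or if VE varies, by neighborhood or household. The interaction test is at most mildly inflated, to about 9-11%.

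All of these sizes rest on assumed cluster sizes and correlations, since the documents give none. The direction for the neighborhood term does not depend on the particular values, provided that some positive residual correlation exists.

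**What to change.** 1. In the main unconditional logistic models, use cluster-robust (sandwich) covariance by neighborhood, derived from the domicile address. Apply it to the neighborhood term, its interaction with vaccination, and the absolute VE intervals and P values. Households sharing an address lie within one neighborhood, so they are covered too.
2. For relative VE, fit booster and eligible two-dose recipients in one model with the same covariance. The plan's formula equals 1 − OR(booster)/OR(two doses), so the contrast and its interval come directly from the model.
3. In Sample Size, state that the ±5-point precision assumes independent people.

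Point estimates from a given absolute-VE model do not change, and no new data are needed. The cost is slightly wider intervals and a little more analysis work. The request is limited to the unconditional models for a practical reason: in version 0.14.6 of the named package, the conditional logit accepts a cluster option but returns unchanged standard errors.
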